## Abstract

**Background::**

The elimination of the pathogenic microorganisms of the periodontal pocket is one of the main points for success in periodontal treatment. The objective of this study is to investigate the clinical and antimicrobial effect of papain-mediated photodynamic therapy in the clinical treatment of periodontal disease.

**Methods::**

Twenty patients with chronic periodontitis will be selected. Patients will be randomly divided into 2 groups (n = 10). Group 1 will receive conventional periodontal treatment and group 2 will receive conventional treatment and antimicrobial photodynamic therapy (PACT). Conventional treatment will consist of oral hygiene guidance, with brushing technique instructions and recommendation of daily flossing. The calculus deposits on the teeth will be removed with ultrasound equipment and curettes for scraping and root planning. The PACT will be performed at the end of each periodontal treatment session, at sites with bags ≥4 mm. PapaMblue photosensitizer will be deposited in the periodontal pockets with a syringe and a pre-irradiation time of 1 minute will be adopted. Then, the laser emitting wavelength of 660 nm, with power of 100 mW, for 2 minutes, radiant exposure of 30 J/cm^2^ and power density of 250 mW/cm^2^ will be applied. Patients will undergo clinical evaluations before treatment (day 1) at 30, 60, and 90 days after the end of treatment; and microbiological evaluations before and immediately after treatment. The distribution of the data within each group and the homogeneity of the variances will be verified. With this information, the most appropriate statistical test in each evaluation will be used. The sample calculation is based on the literature and the significance level of 5% will be adopted.

**Discussion::**

The combination of PACT with methylene blue in a papain gel and the conventional treatment may increase the reduction of bacteria in periodontal pockets.

## Introduction

1

Periodontitis is an inflammatory disease of supporting tissues of the teeth, and it is induced by specific microorganisms and influenced by the immune-inflammatory response of the host. It is characterized by a microbiological association and inflammation that results in loss of the alveolar bone or sustained periodontium. Bleeding is noted when the clinical depth of probing of the periodontal sacs is measured; evident sign of active periodontal disease. The epithelial tissue does not present vascularization, but connective tissue, indicating invasion by periodontopathogens, thus triggering an inflammatory immune response because of bacterial invasion.^[1–3]^

According to the new classification of periodontal diseases, periodontitis is characterized by loss of insertion, alveolar bone resorption, loss of periodontal ligament fibers and root cement contamination. The main factor responsible for periodontitis is the association between strict anaerobic Gram negative bacteria within the periodontal pocket. It also has inflammation in the gingival connective tissue, with a predominance of plasma cells and lymphocytes, there is an increase of proinflammatory cytokines in the site, contributing to tissue destruction and disorganization. The nutrition of the gingival epithelium is also compromised. Thus, cells of the junctional epithelium proliferate and migrate in the apical direction, the main characteristic of the formation of periodontal pockets.^[4]^

The goal of periodontal treatment is to eliminate bacterial deposits by removing the supra and subgingival biofilm, and consequently reducing the excessive inflammatory response. The procedures involve diagnostic steps, followed by biofilm removal and biofilm associated calculation followed by control and maintenance, with the control of etiological agents and risk factors, based on clinical outcomes with non-surgical treatment approaches with the scraping and straightening of the corono-root with manual and ultrasonic instruments, which in addition to the removal of biofilm deposits, contributes to the reduction and modification of biofilm colonizing periodontopathogens. It is noteworthy that patient compliance and contribution is extremely important in the control of health stability in periodontal tissues. Assuming that when biofilm is controlled, it does not accumulate and colonize with more periodontopathogenic species, thus not inducing an inflammatory response related to periodontal disease. The use of lasers for periodontal treatment in noninvasive therapies presents a review of the current state of evidence for the efficacy of these approaches as an adjunctive treatment to mechanical biofilm deposition removal therapy.^[5]^

Photodynamic antimicrobial chemotherapy (PACT) involves the use of a photosensitizer (PS) that is activated by light at resonant wavelength. This phenomena populate the triplet state of the photosensitizer, which at this moment may transfer energy to the medium's oxygen and results in the formation of reactive oxygen species (ROS) such as singlet oxygen, superoxide anion, hydroxyl radical, and hydrogen. These ROS can damage proteins, lipids, nucleic acids, and other cellular components.^[6]^ PACT is a noninvasive modality of treatment, and can be used as an adjuvant to the treatment of periodontitis. For the periodontal treatment, PS binds to the cells of the oral biofilm, and when activated by light they promote the physical disorganization of the biofilm and death of microorganisms by the formation of ROS, and other factors, such as the presence of a high level of metabolic activity.^[7]^

**Table 1 T1:**
[figure not shown]
Laser parameters.

In 2003, a Brazilian formulation was launched in the market called “Papacárie” (Fórmula e Ação, São Paulo, SP, Brazil). The product is a papain based and chloramine gel. This product was presented as an alternative to facilitate the chemical and mechanical removal of dental caries. This gel acts only on infected tissue due to the absence of a plasma antiprotease, alpha 1-antitrypsin, which prevents its proteolytic action in normal tissues. According to the manufacturer, the product facilitates the removal of caries, preserving healthy tissue, can be used without local anesthesia and use of rotary instruments and is indispensable for special patients, such as babies, children, adolescents, and the elderly.^[11,12]^

Papacárie has papain cleansing properties combined with disinfection. Collagen fibrils exposed by the dissolution of surrounding minerals in dentin due to the action of bacteria are susceptible to interaction with the papain-based gel, allowing decayed tissue to be removed with a blunt-tipped instrument. This gel has been successfully used in clinical trials for decayed tissue removal for minimally invasive patients. Papacárie can be safely used in minimal intervention dentistry because it does not cause collagen degradation, which is essential for the dental restoration process.^[10]^

Antimicrobial photodynamic chemotherapy (PACT) is a conventional photodynamic therapy variant that has emerged in minimal dental intervention due to the need to reduce the microbiota in the oral cavity and prevent the progression of caries. PACT combines a photosensitizing agent and an appropriate light wavelength at the maximum absorption peak of the photosensitizer to produce reactive oxygen species that are toxic to bacterial cells. To combine the advantages of papain gel and antimicrobial photodynamic chemotherapy, a change in the composition of Papacárie was made so that this product could be used to remove infected dentin tissue and simultaneously as an antimicrobial agent. The change involved the addition of methylene blue, which is a well-known photosensitizer activated by red light (660–10 nm), giving rise to PapaMBlue. This low cost innovation has been used in an experimental study with positive results. By preventing and treating caries to the best of their ability, dentists can minimize tooth loss and improve patients’ quality of life.^[10,13]^

The aim of this study is to investigate the effect of PapaMBlue-mediated antimicrobial photodynamic therapy (PACT) on the clinical treatment of periodontal disease.

## Methods/Design

2

### Type of study

2.1

This parallel group, controlled clinical trial will be performed with patients with periodontitis who are in attendance at the Nove de Julho University Dental Clinic, São Paulo, Brazil, or are referred for treatment at this center, where all clinical procedures for the study will be performed. It is already approved by the Ethics Committee of the Nove de Julho University (68754517.5.0000.5511). Research participants should read, understand, and sign the Informed Consent Form, approved by the Nove de Julho University Human Research Ethics Committee.

The protocol is in accordance with the 2013 SPIRIT (Standard Protocol Items: Recommendations for Interventional Trials) Statement. The SPIRIT checklist can be found as an additional file and Fig. 1 is the SPIRIT figure. SPIRIT was developed to provide guidance in the form of a checklist of recommended items to include in a clinical trial protocol, to help improve its content and quality.

**Figure 1 F1:**
[figure not shown]
SPIRIT figure as recommended by 2013 SPIRIT statement. SPIRIT = Standard Protocol Items: Recommendations for Interventional Trials.

### Trial registration

2.2

This clinical trial was registered in ClinicalTrials.gov (NCT03855345), first posted and last updated February 26, 2019.

### Sample calculation

2.3

Sample size was calculated based on results of 3 patients and standard deviation of bacterial survival fraction was used on the equation: 
[figure not shown]
*n* is the sample size, *ε* is the maximum error (5%), *σ* is the experimental standard deviation, and Zγ is confidence interval that we expect (95%), with *Z* score at 1.96. Experimental data demonstrated that we need at least 5 patients per group to achieve a probability of 95% to be right.

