### Recruitment and randomization

2.4

Patients with periodontitis who are in attendance at the Nove de Julho University Dental Clinic or are referred for treatment at this center will be recruited. As they will already be in treatment, we expect adherence to be easier. Patients will be randomly divided into 2 groups (n = 10). Group 1 will receive conventional treatment and Group 2 will receive conventional treatment and antimicrobial photodynamic therapy (PACT). The distribution in the experimental groups will be random, and a draw will be made with numbers. As the numbers are drawn, they will make up the experimental groups. Brown envelopes will be identified with each number and, inside them, will be inserted a sheet containing the information of the experimental group, according to the order obtained in the draw. Envelopes will be sealed and remain sealed in numerical order in a safe place until the time of the procedures.

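### The sample-size statement promises 95% assurance for a two-arm comparison from terms that contain no between-group difference and no power

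*Protocol article*

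**What the plan says.** Section 2.3 (Sample calculation) gives the basis as follows: "Sample size was calculated based on results of 3 patients and standard deviation of bacterial survival fraction was used on the equation". The equation is a figure that is not shown, but the text defines its symbols: n is the sample size, ε a maximum error of 5%, σ the observed standard deviation (no value given), and Zγ the 95% confidence term with a score of 1.96. The conclusion is: "Experimental data demonstrated that we need at least 5 patients per group to achieve a probability of 95% to be right".

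Section 2.4 (Recruitment and randomization) plans 10 patients in each of two arms, conventional treatment with or without PACT. Section 3.1 names reduction in CFUs as the primary outcome, and section 3.5 sets a 5% significance level.

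The Methods part of the abstract gives a different basis for the sample size: "The sample calculation is based on the literature and the significance level of 5% will be adopted".

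**The concern.** The trial compares two randomised arms. A sample size for that purpose rests on a between-group difference, a standard deviation, a significance level and a power. The terms in section 2.3 include neither the difference nor the power. What remains fits the question of how many observations are needed to estimate one mean to within ε with 95% confidence. To describe the result as enough patients "to achieve a probability of 95% to be right" moves a confidence level for one mean onto the conclusion of a comparison.

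At stake is how the result is read. Anyone who accepts the assurance at face value could treat a non-significant comparison as firm evidence that PACT adds nothing, although no such property has been shown. The inputs are also weak: the standard deviation comes from 3 patients, and the abstract and section 2.3 disagree about where the calculation comes from.

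**Working it through.** **Inputs from the protocol article.** ε = 5, Z = 1.96, stated minimum n = 5 per group, σ estimated from 3 patients (section 2.3); planned n = 10 per group (section 2.4); α = 5% (section 3.5), taken as two-sided, in line with Z = 1.96.

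**Assumptions.** The equation is n = (Zσ/ε)², which fits the listed symbols. σ is in the same units as ε. Under this formula ε/σ is fixed by n, so the power figures in step 2 do not depend on the unit.

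**1. The plan's own figure.** Because σ has no stated value, n = 5 cannot be reproduced independently. The formula can only be inverted: σ = ε√n/Z.
- Formula gave exactly 5: σ = 5 × √5 / 1.96 = 5.70.
- Formula gave just over 4 and was rounded up to 5: σ just over 5 × √4 / 1.96 = 5.10.

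So 5.10 < σ ≤ 5.70.

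**2. Power for a comparison, for scale.** Take a between-group difference δ equal to the 5-point error. This is a benchmark for this check, not a target that the protocol states. The standardised difference is d = δ/σ, which is 5/5.70 = 0.877 or 5/5.10 = 0.980. The power is that of a two-sided 5% two-sample t-test (noncentral t).

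| Per group | σ = 5.70 | σ just over 5.10 |
|---|---|---|
| 5 | 23.1% | 27.7% |
| 10 | 45.8% | 54.5% |

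The normal approximation gives 28–34% with 5 per group and 50–59% with 10. One-sided 5% t-tests give 35–41% and 60–68%. None of these reaches 80%.

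**3. Larger differences.** On the same back-solved σ, 10 per group has 96–99% power for a difference of 10 points. The difference detectable with 80% power at 10 per group is 6.8 to 7.6 points.

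**4. Results that need neither σ nor the inferred formula.** For a two-sided 5% two-sample t-test:
- 5 per group has 95% power only for a standardised difference of 2.62;
- 10 per group has 80% power for a standardised difference of 1.32.

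The protocol states no effect of either size.

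**5. Precision of a standard deviation from 3 patients.** With 2 degrees of freedom and normal data, the 95% limits as multiples of the estimate are √(2/7.378) = 0.52 and √(2/0.0506) = 6.28. In the assumed formula n scales with σ². Starting from 5, the same calculation would give 5 × 0.521² = 1.36, so 2, up to 5 × 6.285² = 197.5, so 198.

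**6. Source of the calculation.** The abstract says the literature; section 2.3 says 3 patients. No passage reconciles them.

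**The case against.** The strongest reply concerns the power figures. The equation is not shown, σ is not stated, and ε is called a maximum error, never a target difference. A reader might infer from the table that the trial is underpowered, at 23% or 46%, and can find only very large effects. The documents do not support that. The figures depend on an inferred formula, 23% and 46% are the low ends of their ranges, and no passage says that a 5-point difference is the one sought. Nor does any passage show that 7 or 8 points of survival fraction would be large for this outcome. The imprecision in step 5 applies here too: across those multipliers of σ = 5.70, power for 5 points at 10 per group runs from about 6% to 94%. All of this stands, and it is why the figures serve only as a conditional range.

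A second reply is that 5 is a floor and 10 are planned. That disposes of one further criticism, the use of Z rather than t at n = 5. At n = 10 the t-based half-width for one mean is 2.262 × σ/√10, about 3.6 to 4.1 points, inside the 5-point error. It does not rescue the assurance, because planning 10 supplies neither a difference nor a power.

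Third, the abstract may mean that the formula came from the literature and the standard deviation from the 3 patients. That is possible, but the text does not say so, and a clarification settles it.

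None of these replies supplies the missing terms.

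**Conclusion.** The statement is wrong as written. The terms listed in section 2.3 belong to a precision calculation for one mean, so the 95% is a confidence level and not the probability that a two-arm comparison reaches the right answer. This conclusion rests on the symbol definitions in the text; the only gap is the equation that is not shown.

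The size can be given only conditionally. If the formula is the one assumed and it gave 5, power for a difference as small as 5 points is about 23–28% with 5 per group and 46–55% with 10, and it is higher for larger differences. No arithmetic error in the 5 itself is shown, since it can be neither reproduced nor refuted. The imprecision of the standard deviation (0.52 to 6.3 times the estimate) assumes normal data. The disagreement between the abstract and section 2.3 about the basis is textual and needs no assumption.

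**What to change.** In section 2.3, delete the sentence that promises 95% assurance with 5 per group. Keep 10 per group and state what that size offers, for example: with 10 patients per group, a two-sided 5% two-sample t-test has 80% power for a standardised difference of about 1.32; the standard deviation was taken from only 3 patients and is therefore imprecise.

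Make the abstract and section 2.3 name the same basis, or say which part came from the literature and which from the 3 patients.

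The cost is wording only. Enrolment does not change. The stated assurance becomes less favourable.

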### Recruitment and randomization

2.4

Patients with periodontitis who are in attendance at the Nove de Julho University Dental Clinic or are referred for treatment at this center will be recruited. As they will already be in treatment, we expect adherence to be easier. Patients will be randomly divided into 2 groups (n = 10). Group 1 will receive conventional treatment and Group 2 will receive conventional treatment and antimicrobial photodynamic therapy (PACT). The distribution in the experimental groups will be random, and a draw will be made with numbers. As the numbers are drawn, they will make up the experimental groups. Brown envelopes will be identified with each number and, inside them, will be inserted a sheet containing the information of the experimental group, according to the order obtained in the draw. Envelopes will be sealed and remain sealed in numerical order in a safe place until the time of the procedures.

#### Inclusion criteria

2.4.1

The patient should have periodontitis.Have at least 10 teeth present, with at least ≥2 non-adjacent interproximal sites with 1 to 2 mm insertion loss. Presence of a clinical probing depth of at least 4 mm and clinical signs of inflammation, probing bleeding >10%.^[1,14–16]^The patient should be undergoing periodontal treatment at the Nove de Julho University Dental Clinic, institution where this research will be performed. All patients will be treated according to the protocol recommended by the American Academy of Periodontics (AAP, 2001).Patients with a minimum age of 18 years will be recruited.

#### Exclusion Criteria

2.4.2

Smokers or former smokers who discontinued the habit <12 months prior to selection;Uncontrolled diabetes;Anemia;Cancer;Pregnant women;Use of antibiotics in the last 6 months;Use of anti-inflammatory in the last 3 months;Coagulation disorder (use of anti-coagulant, presence of liver diseases, thrombocytopenia, and immunosuppression);Patients under orthodontic treatment;Patients who maintain a biofilm index >25%.

## Evaluations and outcomes

3

### Conventional treatment

3.2

Treatment will consist of oral hygiene guidance, brushing technique instructions, and daily flossing recommendation. All patients will receive the demonstration of oral hygiene techniques. Calculus deposits on the teeth will be removed with ultrasound equipment and root scraping and straightening curettes (American Academy of Periodontology, 2001). After the use of ultrasound and curettes, a bicarbonate jet will be used to remove dental biofilm. Treatment will be performed in 2 to 4 sessions under local anesthesia (2% mepivacaine with 1:100,000 norepinephrine). Gracey periodontal curettes (numbers 3/4, 7/8, 11/12, and 13/14) and Mc Call will be used to remove dental calculi. Other biofilm retaining factors, such as carious lesions, condemned teeth, and maladaptive restorations, will be removed during these periodontal treatment sessions.

### Antimicrobial photodynamic chemotherapy

3.3

PACT will be performed at the end of each periodontal treatment session by a second evaluator at sites with pockets ≥4 mm. The PapaMBlue photosensitizer (F&A Ltda, Sao Paulo, Brazil) will be deposited into the pouches with a syringe, with the bottom of the pouch applied in a coronal direction, and a 1-minute pre-irradiation time will be adopted so that the drug can stain. All bacterial biofilm (according to manufacturer's information). Then, the laser will be applied emitting wavelength of *ʎ* = 660 nm, with power of *P* = 100 mW. The laser will be applied to the mucosa over the oral epithelium with an optical fiber. Irradiation will be performed until the entire periodontal pocket is illuminated for 2 minutes at each spot. Each irradiation point will be of approximately 0.4 cm^2^, which will result in an energy density of 30 J/cm^2^ within 2 minutes of irradiation. The irradiation will have a constant power density of 250 mW/cm^2^. All laser parameters can be found in Table 1.

### Microbiological evaluation

3.4

The microbiological examination will be performed from subgengival biofilm samples collected from the periodontal pockets. Two collections will be performed at each experimental site before irradiation, and immediately after the irradiation procedures. For the collection of the subgingival biofilm, the relative isolation of the teeth with cotton rollers will be done, the supragingival biofilm will be removed with sterile gauze, and the subgingival biofilm sample will be obtained by inserting a tip of sterile absorbent paper (no. 30) in the interior of the periodontal pocket, being held in place for 30 seconds. The tips will be removed and stored in properly identified sterile plastic microtubes, each tube containing 1 mL of sterile Brain Heart Infusion (BHI) culture medium will be conditioned on ice and analyzed immediately after collection.

The samples will be used to determine the CFUs (Colony Forming Units). Each tube with 1 mL BHI will be vortexed and will go through serial dilution of 10^−1^ to 10^−5^ times the original concentration. Aliquots of 10 μL in 5 dilutions will be seeded as striations on the surface of blood agar in Petri dishes. The plates will be incubated at 37 °C for a period of up to 72 hours under anaerobic conditions to evaluate recovered total bacteria. After this period, the CFU will be counted and the data will be submitted to statistical analysis.

### Statistical analysis

3.5

The distribution of the data within each group and the homogeneity of the variances will be verified. With this information, the most appropriate statistical test in each experiment will be used. The significance level of 5% will be adopted.

